## Abstract

Natural reduced water is natural water that contains active hydrogen and reduces oxidation. It is rare in the world, and in Japan, it is produced in the Hita area of Oita Prefecture (Hita Tenryosui water). Previous studies in humans have examined the effects of natural reduced water on diabetes, which is one of the known risks for dementia. Animal studies of natural reduced water have revealed anti-obesity and anti-anxiety effects. However, the effects of natural reduced water on cognitive function, body composition, and psychological function in humans are unknown. Therefore, we investigated the relationship between these items in elderly people who continuously consume natural reduced water. In this study, we recruited participants aged between 65 and 74 years. The participants were randomly and blindly assigned to a natural reduced water (Hita Tenryosui water) group or a control (tap water) group and drank 1 L of water daily for 6 months. Cognitive function, body composition, and psychological function were measured before and after the 6-month intervention period.

## 1. Introduction

In the world, there are natural reduced waters that contain active hydrogen, such as Nordenau water in Germany and Tracote water in Mexico. In Japan, Hita Tenryosui water is known as natural reduced water, and is produced in the Hita Basin in northern Kyushu. Hita Tenryosui water is slightly alkaline (pH 8.3) and contains high concentrations of silicic acid, sodium, potassium, and hydrogen carbonate ion. The mineral composition of Hita Tenryosui water is shown in Figure 1.

Various risks of dementia have been considered, one of which is diabetes. In a meta-analysis of cohort studies, participants with diabetes had a significantly higher incidence of Alzheimer’s disease than those without diabetes [1]. In other meta-analyses, diabetes was associated with increased risks of progression of mild cognitive impairment (MCI) to dementia, and in participants with diabetes, a longer duration of diabetes and the presence of retinopathy were associated with an increased risk of progression from MCI to dementia [2]. In addition, the development of diabetes is associated with oxidative stress, and oxidative stress is a result of overproduction of oxidative-free radicals and associated reactive oxygen species (ROS) [3]. On the other hand, natural reduced water has been experimentally shown to scavenge ROS in cells [4]. The mechanisms of action of reduced water for scavenging ROS are considered to be complicated. Natural reduced water may have some active agents such as active hydrogen, hydrogen anions, hydrogen molecules, mineral nanoparticles, and mineral nanoparticle hydrides [5]. In an animal study, mice treated with alloxan, which promotes the development of diabetes, were administered natural reduced water, which suppressed their blood glucose levels [6]. Furthermore, in a human study, diabetic patients who consumed natural reduced water for 2 months had their fasting blood glucose levels reduced [6]. Therefore, we investigated the relationship between the maintenance or improvement of cognitive function and the consumption of natural reduced water in this study.

Previous research has shown that natural reduced water can improve symptoms in patients with hyperlipidemia [6]. In addition, in animal experiments, continuous drinking of natural reduced water showed anti-obesity effects [7]. There is evidence in clinical surveys linking obesity (or metabolic diseases) to gut microbiota fluctuation. Moreover, Hita Tenryosui water is known to change gut microbiota in animal experiments [7]. On the other hand, natural reduced water increased the expression of aquaporin, a membrane protein that specifically allows water molecules to pass through [8]. Aquaporins in the rat kidney have also been shown to play an important role in body water homeostasis [9]. Therefore, we hypothesized that natural reduced water would change body composition, such as body fat and body water content.

In addition, it has been confirmed that natural reduced water suppresses mental anxiety in mice [10]. When mice were fed natural reduced water for 6 months, urinary 8-hydroxy-2′-deoxyguanosine and blood urea nitrogen levels, which are used as biomarkers to detect anxiety, decreased. Moreover, natural reduced water exhibited anxiolytic-like effects in the conditioned fear and elevated plus maze tests. Hita Tenryosui water (natural reduced water) contains a lot of active hydrogen and reduced free radical production [4]. Stress related to anxiety was reported to be associated with increased free radical production, which natural reduced water may suppress [11]. In a 4-week human intervention experiment, natural killer (NK) cell activity was significantly higher in the group receiving natural reduced water than in the group receiving tap water [8]. Other previous studies have examined the relationship between NK cell activity and depressive tendencies. NK cell activity was reduced in depressed patients with a hip fracture compared with controls at 6 weeks post-fracture. Serum cortisol levels were also elevated in depressed patients compared with those in non-depressed patients [12]. Therefore, we examined the relationship between natural reduced water and psychological functions such as anxiety or stress level.

Based on these previous studies, we hypothesized that the continuous consumption of natural reduced water may affect cognitive function, body composition, and psychological function, and we tested this hypothesis.

## 2. Methods

### 2.1. Study Design

This study was a double-blind, randomized controlled trial that employed a design to measure cognitive function before and after a 6-month intervention for the natural reduced water and tap water groups. The purpose of this study was to determine the relationship between the continuous consumption of natural reduced water and cognitive function, body composition, and psychological function. In terms of cognitive function, we assessed executive function, attention function, short-term memory, and verbal fluency. In addition, we tested body composition (e.g., body fat and body water content) and psychological function (e.g., anxiety and stress levels).

### 2.2. Patient and Public Involvement

We recruited participants for this experiment by advertising in a local newspaper. This local newspaper is a weekly publication with a circulation of 450,000 in the Sendai area (Miyagi Prefecture). As this study is aimed at preventing dementia, we focused our recruitment on the age group where most elderly people without dementia are concentrated.

### 2.3. Inclusion Criteria

The inclusion criteria were as follows: (1) age between 65 and 74 years old and (2) healthy elderly people who live independently in daily life.

### 2.4. Exclusion Criteria

Based on previous studies [13,14,15,16], the exclusion criteria for the participants included conditions related to electrolyte abnormalities (such as hyponatremia). The criteria were as follows:
(1)People with a current medical history:–Renal disease;–Cardiac disease;–Liver cirrhosis;–Syndromes of inappropriate antidiuretic hormone (SIADH);–Hypothyroidism;–Diabetes;–Hyperlipidemia;–Mental illness (polydipsia);–Vomiting or diarrhea.(2)People taking oral medications:–Antiepileptic drugs;–Antidepressants;–Diuretics;–Antihypertensive agents;–Antiarrhythmic drugs.(3)People with severe visual or hearing impairment;(4)People who have continuously consumed natural reduced water in the last year.

### 2.5. Water Used for the Intervention

The natural reduced water used in this study was commercially available Hita Tenryosui water. For tap water, we used tap water from Oita Prefecture that had been boiled. Each type of water was poured into plastic bottles at the factory of Hita Tenryo-Sui Co., Ltd. The plastic bottles for both types of water were not labeled, and the same caps were used so that the participants themselves would not know which type of water they were drinking. Each bottle of water was delivered to the participant’s home on a regular basis.

### 2.6. Protocol

The design of this study is illustrated in Figure 2. First, we explained the contents of this study to the participants and obtained their informed consent. We then administered a pre-intervention baseline test to the participants. In this test, we measured cognitive function, body composition, and psychological function. The participants were then randomly divided into the natural reduced water group and tap water group, and the intervention was conducted for 6 months. During the intervention period, participants consumed 1 L of each group’s water daily and wrote down their intake on a list. We would have preferred to set the daily consumption of water to 2 L as in previous studies of Hita Tenryosui water [4], but considering the risk of hyponatremia in internal discussions, we decided to set the amount as 1 L per day. The participants were blinded so that they could not tell which water they were drinking. After the 6-month intervention, a post-intervention examination was conducted. We administered a pre-test and post-test before and after the 6-month period, drawing on other intervention studies of cognitive function [17,18]. This study will investigate the maintenance or improvement of cognitive function in healthy elderly people, not in people with dementia or other illnesses. In addition, previous studies have shown significant improvement in cognitive function in a 6-month intervention study [17,18]. The content of the post-intervention test was the same as that of the pre-intervention test. After the post-intervention test, the participants in the natural reduced water group had a follow-up test 6 months later (12 months after the start of the intervention) and were told not to drink the natural reduced water until the follow-up test. The participants in the tap water group were asked if they wanted to drink natural reduced water, and those who wanted to could drink the same amount as the natural reduced water group after the post-intervention test. Data from people whose water intake is less than 90% of the total will be excluded as dropped data. We will also exclude people who become unable to drink water during the course of the intervention or who start taking medications that meet the exclusion criteria.

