### 2.8. Sample Size

Assuming a significance level (α) of 5%, the effect size at 0.6, and a power of test (1 − β) of 80%, which are all “moderate” levels according to Cohen, the required number of participants was 34 in each group. Six months of intervention, assuming a drop rate of 10%, would require approximately 38 participants, for a total of 76 recruits. We added two more people to each group in case of unforeseen circumstances.

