### 2.9. Statistical Considerations

We conducted a two-factor analysis of variance with group (intervention and control groups) and time (pre-intervention and post-intervention) as factors to examine the relationship between the scores of each measurement item in the intervention and control groups. Using path analysis, we plan to conduct an exploratory analysis to investigate the relationship between each measurement item.

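### Participants are removed after randomisation for low intake, inability to drink or a new listed drug, so the article's only between-group analysis is run on a selected set and may be biased

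*Protocol article*

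**What the plan says.** Section 2.6 of the protocol article fixes the order of events. After consent and the baseline test, "The participants were then randomly divided into the natural reduced water group and tap water group, and the intervention was conducted for 6 months". During those 6 months "participants consumed 1 L of each group’s water daily and wrote down their intake on a list", so adherence rests on the participant's own record.

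The same section then sets three removal rules:

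- Low intake: "Data from people whose water intake is less than 90% of the total will be excluded as dropped data".
- Inability to drink, and new drugs: "We will also exclude people who become unable to drink water during the course of the intervention or who start taking medications that meet the" (the quoted sentence ends by referring to the criteria for exclusion at entry).

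The drug list is in Section 2.4: "People taking oral medications:–Antiepileptic drugs;–Antidepressants;–Diuretics;–Antihypertensive agents;–Antiarrhythmic drugs".

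Section 2.9 gives one between-group analysis: "We conducted a two-factor analysis of variance with group (intervention and control groups) and time (pre-intervention and post-intervention) as factors". The article names no analysis of all randomised participants, either as the main analysis or as a sensitivity analysis.

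Section 2.8 allows for losses: "Six months of intervention, assuming a drop rate of 10%, would require approximately 38 participants" per group. Two more per group are then added.

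**The concern.** All three rules act on events after randomisation, and each can be connected with what the trial measures (Section 2.7):

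- **New drugs.** The outcomes include POMS 2 mood scores, the Perceived Stress Scale and body water content. Someone whose mood worsens enough to need an antidepressant leaves the mood comparison. Someone who starts a diuretic leaves the body-water comparison.
- **Low intake.** Drinking and recording a set volume every day for 6 months is a task that may track memory, attention and mood, which are themselves outcomes.
- **Inability to drink.** This may reflect tolerability of the water or a decline in health.

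Removal could also differ by arm. Section 1 describes the study water as slightly alkaline and rich in minerals, and Section 2.5 makes the comparator boiled tap water, so taste or tolerability may differ. The trial also hypothesises that the water changes mood and body water. If it does, drug starts could differ by arm as well.

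At stake is the main benefit of randomising: that a difference between arms can be put down to the water and not to who was left in the data. The rules apply to every outcome. As worded, they would remove people whose 6-month tests were completed.

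**Working it through.** **1. The plan's own sample size.** Inputs from Section 2.8: α 5% (sidedness not stated), standardised effect 0.6, power 80%, 34 per group, 10% drop rate, two extra per group. The formula is n = 2 × ((z for α + z for power) / 0.6)².

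- One-sided: 2 × ((1.645 + 0.842) / 0.6)² = 34.35, close to the stated 34.
- Two-sided: 2 × ((1.960 + 0.842) / 0.6)² = 43.60, which does not reproduce 34.
- Drop-out: 34 / 0.9 = 37.8, so 38 per group. Adding 2 gives 40 per group, 80 in total.

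The stated figure is thus approximately a one-sided one, so power is shown on both bases below.

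**2. Room for removals.** 40 − 34 = 6 per group, and 6 / 40 = 15%. Withdrawals, low intake, inability to drink and drug starts must together stay within that margin for 34 to remain.

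**3. Power if more are removed** (t-test, effect 0.6). The 20% and 30% rates are assumptions: 40 × 0.8 = 32 and 40 × 0.7 = 28.

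| n per group | One-sided 5% | Two-sided 5% |
|---|---|---|
| 40 | 84.5% | 75.5% |
| 36 (10% removed) | 80.9% | 70.9% |
| 34 (planned) | 78.9% | 68.4% |
| 32 (20% removed) | 76.7% | 65.6% |
| 28 (30% removed) | 71.6% | 59.7% |

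**4. Bias with no true effect.** In a group-by-time analysis the treatment effect is a difference in change, so the gap that matters is in change from baseline. If a fraction p of an arm is removed and those removed change worse than those retained by a gap g (in SD), the retained mean is too high by p × g. The bias in the difference between arms is g × (p₁ − p₀).

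Assumed, not in the documents: removal of 25% against 10%, and g from 0.5 to 1.0 SD.

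- g = 0.5: 0.5 × (0.25 − 0.10) = 0.075 SD.
- g = 1.0: 1.0 × (0.25 − 0.10) = 0.15 SD.
- Equal removal with the same g: g × 0 = 0.

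If the planned 0.6 is on the same scale, these are 0.075 / 0.6 = 12.5% and 0.15 / 0.6 = 25% of it. The sign depends on which arm loses more people and on whether they do worse or better.

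**5. A second illustration.** Simulation with no true effect, 40 per arm, the least adherent removed, and an assumed correlation of 0.3 to 0.5 between adherence and outcome:

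| Removed, by arm | Bias (SD) | One-sided type I error | Two-sided type I error |
|---|---|---|---|
| 10% v 10% | 0 | about 0.05 | 0.05 to 0.06 |
| 15% v 5% | 0.05 to 0.08 | 0.08 to 0.11 | 0.06 to 0.07 |
| 20% v 0% | 0.11 to 0.18 | 0.11 to 0.18 | 0.07 to 0.11 |

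The one-sided column counts false results in favour of the arm with more removals.

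**The case against.** The best defence is that removal is likely to be similar in the two arms. Both drink 1 L of water a day from unlabelled bottles with the same caps, and participants are blinded (Sections 2.5 and 2.6). Nothing in the article points to 25% against 10%. Equal removal with the same relation to outcome gives no bias, and a stable gap already present at baseline largely cancels in a comparison of changes. All of this stands: it limits the likely size, and the bias figures are illustrations only. It does not secure equality, because drug starts and tolerability could still differ by arm.

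It may also be said that an unseen analysis plan could add an all-randomised analysis. It could, but it would have to depart from a removal rule that the article states outright.

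Several stronger readings are tempting and are not supported:

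- A reader might infer that exclusions alone take power from 80% to 66% or 60%. Two-sided power is already 75.5% at 40 and 68.4% at the planned 34. Most of the gap from 80% to 66% is the separate question of sidedness. On either basis, going from 34 to 32 costs 2 to 3 points.
- A reader might infer that the evaluable number will fall below plan. That is conditional. The article calls low adherers dropped data, so the 10% may already count them, and there is a margin of 6 per group.
- A reader might infer that harms are concealed. The text removes people from the data; it does not say that exclusions or adverse events go unreported.
- A reader might convert 90% into a number of missed days. The rule concerns total intake, so a steady daily shortfall would trigger it too.

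**Conclusion.** The point holds as a design flaw that the article states, not as a missing detail. The one between-group analysis it describes would be run on participants selected by intake, ability to drink and new medication after randomisation. It would be too strong to call the comparison non-randomised or to say that bias is certain: the arms were formed by randomisation, but their balance is no longer guaranteed in the set analysed. Bias arises if removal differs by arm, or relates to outcome differently by arm, and its direction is unknown.

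Under the assumed 25% against 10% removal and a 0.5 to 1.0 SD gap in change, the bias is 0.075 to 0.15 SD with no true effect, and it is nil if removal and its relation to outcome are equal. The loss of power is secondary: up to 15% removal per arm leaves the planned 34. At 32 or 28 per group, power at 0.6 is 77% or 72% one-sided (66% or 60% two-sided), against 79% (68%) at 34.

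**What to change.** - Make the main analysis all randomised participants in the arm assigned, using their 6-month outcomes whatever their intake or new drugs.
- Invite everyone to the 6-month test that is already planned, including those who stopped drinking or started a listed drug. This concerns keeping outcome data only and must not imply continued intake of study water.
- Handle 6-month tests that are truly missing with a likelihood-based model.
- Keep the 90% and drug-start rules only to define a per-protocol sensitivity set.
- Report the number removed from that set, and the reasons, by arm.

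The cost is a change of protocol and analysis wording, plus one already scheduled visit for people who would otherwise be dropped.

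The statistical downside is some dilution of the effect of full intake. For example, assume 10% of the active arm gains nothing. The effect is then 0.6 × 0.9 = 0.54, and power with all 40 per group is 77.3% one-sided (66.5% two-sided). With 36 per group and the undiluted 0.6 it is 80.9% (70.9%). The per-protocol set still shows the effect of full intake.

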### 2.7. Measurement Items

The measurement items were as follows:(1)Mini-Mental State Examination (MMSE) [19]: The MMSE is a 30-point paper-based test that is used to measure global cognitive function (cut-off point, 23/24).(2)Trail Making Test (TMT) [20]: The TMT is used to measure executive function. This test is a commonly used method for testing attention function. The test consisted of two parts. In part A, participants were instructed to connect 26 numbered circles in ascending order. In part B, participants were instructed to connect numbers and letters in an alternating fashion. The time taken was then measured.(3)Digit Span (DS) [21]: The DS is a subtest from the Wechsler Adult Intelligence Scale-III to assess short-term memory. In this test, the participants had to answer the spoken numbers in the same order. Subsequently, they had to answer in reverse order.(4)Verbal Fluency Test (VFT) [22]: The VFT is used to assess verbal fluency. For the VFT, participants had to write as many words as possible in 60 s. The test consisted of two tasks. The first task was to write a word of a specified category, such as fruits. The second task was to write a word that started with a specified letter.(5)Profile of Mood States 2 (POMS 2) [23]: The POMS 2 assesses the mood states of individuals 13 years of age and older. It yields several scale scores: anger–hostility, confusion–bewilderment, depression–ejection, fatigue–inertia, tension–anxiety, and vigor–activity. We used the shortened version, and there were 35 items.(6)Perceived Stress Scale (PSS) [24]: The PSS is the most widely used psychological instrument for measuring the perception of stress. It is a measure of the degree to which situations in one’s life are appraised as stressful and consists of 14 items.(7)Subjective Happiness Scale (SHS) [25]: The SHS is a four-item scale of global subjective happiness. Two items ask respondents to characterize themselves using both absolute ratings and ratings relative to peers, whereas the other two items offer brief descriptions of happy and unhappy individuals and ask respondents the extent to which each characterization describes them.(8)Body Composition: We measured the participants’ body composition using a body composition analyzer (RD-800; TANITA, Japan). The measurement items included body water content, body fat, and muscle mass.

### 2.8. Sample Size

Assuming a significance level (α) of 5%, the effect size at 0.6, and a power of test (1 − β) of 80%, which are all “moderate” levels according to Cohen, the required number of participants was 34 in each group. Six months of intervention, assuming a drop rate of 10%, would require approximately 38 participants, for a total of 76 recruits. We added two more people to each group in case of unforeseen circumstances.

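### Section 2.8's 34 per group does not give 80% power at effect size 0.6 for a plain two-sided comparison (45 are needed), and the calculations that do lead to about 34 are not the group-by-time test of section 2.9

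*Protocol article*

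**What the plan says.** Section 2.8 (Sample Size) takes a 5% significance level, "the effect size at 0.6" and 80% power, and states that "the required number of participants was 34 in each group". It allows for 10% dropout, so that the trial "would require approximately 38 participants, for a total of 76 recruits", and then adds two people per group, making 40 per group and 80 in all. It does not say which test was powered, whether it is one- or two-sided, or on what scale 0.6 is measured.

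Section 2.9 (Statistical Considerations) fixes the analysis: "We conducted a two-factor analysis of variance with group (intervention and control groups) and time (pre-intervention and post-intervention) as factors". Section 2.6 places the baseline test before randomisation and the second test after the 6-month intervention. Section 3 gives the expected directions of effect but states no one-sided test.

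**The concern.** A sample size and a power stated together should follow from the inputs given beside them, for the test that will be run. The usual reading of alpha 5%, effect size 0.6 and 80% power in two groups is a two-sided comparison of means, and that reading does not lead to 34. The F tests of the planned analysis of variance are non-directional, so section 2.9 points the same way.

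The stake is how the result is read. A null finding would be taken as evidence against a 0.6 SD effect with a 20% chance of having missed it. On the plain two-sided reading that chance is 29% to 32%.

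**Working it through.** **Inputs from section 2.8:** alpha 0.05, effect size 0.6 (read as a standardised mean difference d), power 0.80, equal groups, dropout 10%, two extra per group. **Assumed, because not stated:** sidedness, the scale of d, and the pre-post correlation r. Each is varied below.

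**1. Dropout step.** 34 / 0.90 = 37.8, so 38 per group and 76 in total, as stated. With two more per group, 40 are recruited, and 40 × 0.90 = 36 are expected to be evaluable.

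**2. Two-sided two-group comparison.** Normal approximation: n = 2 × [(1.960 + 0.842) / 0.6]² = 43.6, so 44. Exact noncentral t: 44.6, so 45 per group, or 45 / 0.90 = 50 per group recruited. The stated 34 is not reproduced.

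| Evaluable per group | Two-sided power at d = 0.6 | d detectable with 80% power |
|---|---|---|
| 34 | 68.4% | 0.69 |
| 36 | 70.9% | 0.67 |
| 40 | 75.5% | 0.63 |

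**3. Where 34 could come from.**

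- *One-sided 5%.* Normal approximation: n = 2 × [(1.645 + 0.842) / 0.6]² = 34.35. Exact t: 35.04, so 36 per group. Exact one-sided power at 34 is 78.9%. This is close to the stated figure.
- *Repeated-measures ANOVA, between-group main effect.* With f = 0.3 (equivalent to d = 0.6), two measurements and an assumed r = 0.5, the total is 68, exactly 34 per group, with a non-directional F test. This calculation assumes a group difference of 0.6 averaged over both time points. Baseline precedes randomisation, so the groups are expected to be equal there, and an effect of 0.6 present only at 6 months averages to 0.3. The SD of a participant's mean of two scores is √[(1 + 0.5) / 2] = 0.866, so the standardised effect is 0.3 / 0.866 = 0.346. Power for that main effect at 34 per group is about 29%.

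**4. The group-by-time test.** With two time points this equals a two-sided comparison of change scores. For an effect of 0.6 raw-score SD, the standardised effect is 0.6 / √[2(1 − r)].

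| Assumed r | Standardised effect | Needed per group | Power at 34 | Power at 36 |
|---|---|---|---|---|
| 0.3 | 0.507 | 63 | 54% | 56% |
| 0.5 | 0.600 | 45 | 68% | 71% |
| 0.62 | 0.688 | 35 | 80% | 82% |
| 0.7 | 0.775 | 28 | 88% | 90% |

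If 0.6 is already in units of the change-score SD, the r = 0.5 row applies whatever the correlation.

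**5. Baseline-adjusted ANCOVA at 6 months.** The standardised effect is 0.6 / √(1 − r²). At r = 0.5 it is 0.6 / √0.75 = 0.693, giving 80% power at 34 and 83% at 36. At r = 0.3 it is 0.6 / √0.91 = 0.629, giving 72% and 75%.

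**The case against.** The strongest reply is that section 2.8 never says the test is two-sided, that it is a simple two-group comparison, or on what scale 0.6 is measured. On other readings 34 is reasonable. It is within two participants of a one-sided calculation, it is exactly what a repeated-measures main-effect calculation gives, and ANCOVA with r = 0.5 also leads to it. The group-by-time test itself reaches 80% at 34 per group if r is about 0.62. A condensed article may also leave the sidedness and the correlation to a fuller document.

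Much of this stands, and it rules out two stronger readings. A reader might infer that 34 can only be a one-sided figure rounded down. It cannot be pinned down in that way, since two non-directional calculations also yield 34. A reader might also infer that the trial's true power is 68%. The document supports no single value: the group-by-time power at 34 runs from 54% to 88% over r = 0.3 to 0.7, and 36 rather than 34 per group are expected to be evaluable. The absence of a stated correlation is not in itself a fault in an article of this kind, and the wording "which are all “moderate” levels according to Cohen" changes no number, so neither is raised as a defect.

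The reply does not rescue the stated power for the planned test. No one-sided test is declared, and the expected directions in section 3 do not make one. The main-effect route powers a contrast that dilutes the intervention effect. ANCOVA is not the analysis in section 2.9. A correlation of about 0.62 would suffice, but nothing in section 2.8 invokes it.

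**Conclusion.** The point holds in conditional form: section 2.8's pairing of 34 per group with 80% power is wrong as written for a plain two-sided comparison at d = 0.6. The shortfall is 11 per group (45 against 34). Expected power at the planned recruitment is about 71%, and full retention of all 40 would still leave it below 80%. These figures rest on a two-sided 5% test and on d = 0.6 applying either to a simple comparison or to a change score with r of about 0.5. For the group-by-time test more generally, power depends on the correlation as tabulated, and 80% at 34 per group needs r of about 0.62. The calculations that do produce about 34 answer a different question from the test in section 2.9 that measures the intervention effect.

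**What to change.** Restate section 2.8 for the two-sided test. Name the test and the scale of the effect size, and say that 40 recruited per group (36 evaluable) gives about 71% power for d = 0.6, or 80% power for d of about 0.67. Add that this holds for a simple comparison, or for a change score with a pre-post correlation of about 0.5.

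Alternatively, make baseline-adjusted ANCOVA at 6 months the analysis in section 2.9 and base section 2.8 on it, with the correlation written down as an assumption. Show the sensitivity too, because the document does not support any particular correlation: 34 and 36 evaluable per group give 80% and 83% power at r = 0.5, but 72% and 75% at r = 0.3.

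Neither route needs more participants. The first costs a less favourable stated power. The second avoids that only if the assumed correlation is defensible, and it changes the named analysis.
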